# Comparison of the effect of modified intermittent fasting and daily calorie restriction on sleep quality, anthropometric data, and body composition in women with obesity or overweight: study protocol of a randomized controlled trial

**DOI:** 10.1186/s13063-023-07070-0

**Published:** 2023-01-16

**Keywords:** Sleep quality, Intermittent fasting, Anthropometric indices, Pittsburgh Sleep Quality Index, Weight loss

## Abstract

**Background:**

Sleep disturbances are common in nearly one-third of adults. Both low quality of sleep and sleep time could be related to increased obesity. An increase in visceral adipose tissue can result in the secretion of inflammatory cytokines. Inflammatory cytokines can lead to a disturbance of the sleep-wake rhythm. Therefore, weight loss may improve sleep quality and duration. Intermittent fasting diet as a popular diet reduces body weight and improves anthropometric indices. This study is performed to further investigate the effect of a modified intermittent fasting diet on sleep quality and anthropometric indices.

**Methods:**

This is an open-label randomized controlled trial to evaluate the effect of daily calorie restriction (control) and modified intermittent fasting (intervention) on sleep quality, anthropometric data, and body composition in women with obesity or overweight for 8 weeks. Fifty-six participants will be classified using stratified randomization based on body mass index (BMI) and age. Then, participants will be assigned to one of the two groups of intervention or control using the random numbers table. The sleep quality, daytime sleepiness, and insomnia will be evaluated by using the Pittsburgh Sleep Quality Index (PSQI), the Epworth Sleepiness Scale (ESS), and the Insomnia Severity Index respectively. The primary outcomes chosen for the study were as follows: the difference in sleep quality, daytime sleepiness, insomnia, BMI, fat-free mass (FFM), body fat mass, waist circumference, and waist-to-hip ratio from baseline to 8 weeks. Secondary outcomes chosen for the study were as follows: the difference in hip circumference, the visceral fat area, percent body fat, soft lean mass, skeletal muscle mass, extracellular water ratio, and total body water from baseline to 8 weeks.

**Discussion:**

This study will investigate the effect of intermittent fasting intervention compared with daily calorie restriction on sleep quality and anthropometric indices. The information gained will enhance our understanding of fasting interventions, which can be used to improve clinical dietary recommendations. The findings will help to disclose as yet the unknown relationship between diet and sleep quality.

**Trial registration:**

Iranian Registry of Clinical Trials IRCT20220522054958N3. Registered on 8 July 2022. https://www.irct.ir/trial/64510.

## Background

Sleep disturbances affect a great number of the population. Nearly one-third of adults have one or more symptoms of sleep disturbances. Women and older people suffer more from insomnia than others. Some studies indicated that sleep quality is related to food intake [1]. Low sleep quality affects subjects with severe obesity and with moderate obesity [2, 3]. Inflammatory cytokines can lead to a disturbance of the sleep-wake rhythm [3]. Therefore, weight loss can improve sleep quality and duration [4]. Gangwisch et al. [5] in the National Health Examination Survey (NHANES) reported that participants with higher body mass index (BMI) had lower sleep duration than individuals with lower BMI.

Calorie restriction as first-line therapy has been considered for weight loss in obese patients [6]. Adherence to daily calorie restriction diets is low because the energy requirement is restricted every day [7]. Recently, intermittent fasting has emerged as a new diet for weight reduction. It increases metabolic health in addition to losing body weight [8]. Several studies demonstrated a 3 to 7% reduction in body weight under a fasting diet within 8 to 12 weeks [9]. What has remained unclear is whether intermittent fasting or calorie restriction will further improve anthropometric indices [6]. Other studies propose that alternate-day fasting may result in the preservation of fat-free mass and reduction of visceral adipose tissue in comparison with calorie restriction [10]. In a systematic review conducted by Trepanowski et al. [6], an alternate-day fasting diet and similar interventions reduced body weight similar to daily calorie restriction diets but reduced waist circumference greater than daily calorie restriction [6, 11]. They showed that both calorie restriction and alternate-day fasting increased the fat-free mass, and did not have an effect on the visceral adipose tissue [6]. Hutchison et al. [12] reported that intermittent fasting for 8 weeks resulted in greater fat mass and weight loss compared with calorie restriction in women with obesity and overweight. Previous studies indicated that calorie restriction improves sleep quality [13–15], but there are very limited studies on the effect of fasting on sleep quality. In a recent study by Teong et al. [16], no significant difference was seen between calorie restriction and intermittent fasting on sleep quality in women with obesity or overweight [16]. Therefore, this study will be performed to address this knowledge gap and further investigate the effect of a fasting diet on sleep and anthropometric indices.

## Methods/design

### Study design and participants

This is a randomized, controlled, parallel-group trial to compare the effect of a modified intermittent fasting diet and daily calorie restriction diet on sleep quality and anthropometric indices in women with obesity or overweight over 8 weeks. The framework of the trial is superiority. Participants will be selected from the Health Centers of Kashan University of Medical Sciences by simple random sampling. Participants will be randomly assigned into two groups, daily calorie restriction (control) and fasting (intervention). The protocol was approved by the Ethics Committee of Kashan University of Medical Sciences (IR.KAUMS.MEDNT.REC.1401.046) and was registered at the Iranian Registry of Clinical Trials (IRCT20220522054958N3). All participants will give written consent before any study-related procedure. Inclusion criteria include obese or overweight (40 >BMI ≥25) women between 18 and 50 years old. Exclusion criteria include breastfeeding; pregnancy; having chronic diseases such as heart disease, hypertension, diabetes, and gastrointestinal disorders; smoking; weight loss of 1 to 2 kg in the past month; alcohol abuse; following a specific diet or taking a specific medication; overnight shifts; taking dietary supplements; and having mental or psychological diseases. The obese or overweight (40 >BMI ≥25) women between 18 and 50 years old will be included in the study, provided they meet the inclusion criteria.

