### Sample size calculation

We based our sample size calculation on fat-free mass (FFM) data of a previously published randomized controlled trial [17]. The mean and standard deviation of FFM were 63.4 and 3.4 (kg) in the intervention group and 66.9 and 4.9 (kg) in the control group. To detect a clinically significant difference in the outcome measures (sleep quality, daytime sleepiness, insomnia, BMI, FFM, body fat mass, waist circumference, waist-to-hip ratio, hip circumference, the visceral fat area, percent body fat, soft lean mass, skeletal muscle mass, extracellular water ratio, and total body water) with an alpha error of 5% and power of 80%, 23 women will be needed in each group. We presume a drop-out rate of 20%, based on clinical study experience, and thus 28 women will be recruited in each group.$$n=\frac{{\left(Z1-\frac{\alpha }{2}+Z1-\beta \right)}^2\left({\sigma}_1^2+{\sigma}_2^2\right)}{\left({\mu}_1-{\mu}_2\right)}$$

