### Insomnia

The Insomnia Severity Index has seven items that evaluate the severity of sleep-onset (initial), early morning awakening (terminal) problems, sleep maintenance (middle), satisfaction with current sleep pattern, noticeability of impairment attributed to the sleep problem, interference with daily functioning, and level of distress caused by the sleep problem. Each item is rated on a 0–4 scale (0 indicating no problem and 4 indicating a very severe problem) with a total score ranging from 0 to 28. The Insomnia Severity Index total scores are categorized as 0–7: not clinically significant insomnia; 8–14: subthreshold insomnia; 15–21: moderate insomnia; and 22–28: severe insomnia [22].

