### Statistical assessment

To investigate if the data follows a normal distribution, we will use the Kolmogorov-Smirnov test. To compare qualitative data between the two groups, a chi-square test will be used. An independent t-test will be used to determine differences in quantitative data between groups. In non-parametric conditions and parametric conditions, the Wilcoxon test and paired *t*-test, respectively, will be used to compare the mean of quantitative variables within the group before and after the intervention. To compare the mean between the two groups, the Mann-Whitney test and *t*-test for non-parametric conditions and parametric conditions, respectively, will be used. Analysis of covariance will be utilized to determine the difference in data changes between the 2 groups at the end of the study. The adjusted *p-*values corresponding to each statistical test will be used to investigate the intervention effects by using the Bonferroni correction to analyze multiple outcomes. Data analysis will be done with SPSS software. We plan to conduct two subgroup analyses, both with strong biological rationale and possible interaction effects. Multiple regression model and analysis of covariance (ANCOVA) will be used to evaluate whether specific variables are confounders for the treatment effect and whether the treatment effect interacts with specific covariates.

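### The 80% power claimed for the three sleep outcomes is unsupported: it comes from fat-free mass data alone, and no sleep problem is required at entry

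*Protocol article*

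**What the plan says.** Under Sample size calculation, the protocol article names its only source of data: "We based our sample size calculation on fat-free mass (FFM) data of a previously published randomized controlled trial". The values are "The mean and standard deviation of FFM were 63.4 and 3.4 (kg) in the intervention group and 66.9 and 4.9 (kg) in the control group". From these it moves to a power statement that covers all 15 outcomes, beginning with the sleep measures: "To detect a clinically significant difference in the outcome measures (sleep quality, daytime sleepiness, insomnia, BMI, FFM, body fat mass", and so on through the list, "with an alpha error of 5% and power of 80%, 23 women will be needed in each group". No difference, SD or baseline score on any sleep scale appears anywhere in the article.

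The Primary outcomes section lists change in PSQI, ESS and ISI among eight primary outcomes.

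Under Study design and participants, the entry rule is "Inclusion criteria include obese or overweight (40 >BMI ≥25) women between 18 and 50 years old". No PSQI, ESS or ISI threshold is set. The exclusions include night-shift work and mental or psychological disease.

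The only prevalence figure is in the Background and refers to adults in general: "Nearly one-third of adults have one or more symptoms of sleep disturbances". The same section says that women have more insomnia and that sleep quality is poor in obesity. The Study hypothesis section expects more sleep disorders in this population. Neither section gives a rate for it.

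The Insomnia section grades ISI totals as "0–7: not clinically significant insomnia; 8–14: subthreshold insomnia; 15–21: moderate insomnia; and 22–28: severe insomnia".

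**The concern.** A power figure belongs to one effect, one SD and one population. Here a figure worked out in kilograms of FFM is extended to three questionnaire scores without any input for them.

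The entry rule adds a second difficulty. On PSQI and ISI a low score means no problem and the scale stops at 0. A woman who starts near that end has little room to improve. The planned comparison averages over the whole arm, so if few women have disturbed sleep, the mean difference between diets shrinks. This would matter even if the sample size had been based on a sleep effect, should that effect come from a study of poor sleepers.

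Sleep leads the title, the aim and the list of primary outcomes. The Background cites an earlier trial that found no significant difference in sleep quality between these two types of diet. A second null result, backed by a stated 80% power, would be read as confirmation although the document gives no ground for that power.

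**Working it through.** **Inputs from the document (Sample size calculation).** FFM means 63.4 and 66.9 kg, difference 3.5 kg; SDs 3.4 and 4.9 kg; alpha 5%, taken as two-sided because the formula uses Z(1−α/2); power 80%; 23 women per group.

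**Step 1: reproduce the plan's figure.**
- Sum of variances: 3.4² + 4.9² = 11.56 + 24.01 = 35.57.
- n = (1.960 + 0.842)² × 35.57 / 3.5² = 7.849 × 35.57 / 12.25 = 22.79, rounded up to 23.
- The printed formula lacks the square in the denominator. As printed it gives 7.849 × 35.57 / 3.5 = 79.8, so the 23 comes from the standard squared form.
- Power at 23 per group: 80.4% by the normal approximation, 78.6% by the noncentral t.

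The 23 is therefore right for FFM, and no sleep quantity enters it.

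**Step 2: the standardised effect behind it.** Root-mean-square SD = √(35.57/2) = 4.217 kg; 3.5 / 4.217 = 0.83. Extending the 80% to sleep amounts to assuming a 0.83 SD difference between diets on each sleep scale.

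**Step 3: illustration of dilution.** Four assumptions, none of them in the document:
- the 0.83 holds on the sleep scales for women with disturbed sleep;
- these women are a share f of those enrolled (one-third echoes the figure for adults in general; one-half and two-thirds allow for worse sleep in this population);
- the effect in the other women is zero;
- the SD is unchanged.

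The whole-group effect is then 0.83 × f, with noncentrality 0.83 × f × √(23/2) and 44 degrees of freedom:

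| Share f | Whole-group effect | Power, two-sided 5% |
|---|---|---|
| 1/3 | 0.277 | 15% |
| 1/2 | 0.415 | 28% |
| 2/3 | 0.553 | 45% |
| 1 | 0.830 | 79% |

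**Step 4: how firm is that range?** Relax one assumption at a time (noncentral t, 23 per group):

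| Change | f = 1/3 | f = 1/2 | f = 2/3 |
|---|---|---|---|
| SD 70% as large (effect 0.83f / 0.7) | 26% | 50% | 75% |
| Half effect in good sleepers (effect 0.83 × (f + (1−f)/2)) | 45% | 54% | 63% |

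With a still smaller SD the loss can vanish. At half the SD, the normal approximation gives 47%, 80% and 96%.

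All these figures use the plan's unadjusted 5%. The Bonferroni correction in the Statistical assessment section would lower them. Over eight primary outcomes (alpha 0.05/8 = 0.00625), the Step 3 scenario gives about 3% to 17%, and 48% with no dilution.

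**Step 5: what a subgroup could show.** At f = 1/3, about 23/3 = 7.7 women per arm have disturbed sleep. With the full 0.83 effect the noncentrality is 0.83 × √(7.67/2) = 1.63, and power within that subgroup is about 33%.

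**The case against.** Several points on the other side are sound.

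- **The dilution figures are a scenario.** A reader might infer that power on the sleep outcomes falls to 15–45%. The document does not support that as a result: it gives neither a sleep effect, nor a sleep SD, nor a share of poor sleepers, and Step 4 shows that the answer moves widely.
- **It is not shown that most enrolled women sleep well.** The one-third refers to any symptom in adults generally, and the article expects worse sleep in this population. The two-thirds row itself supposes that most women do have disturbed sleep. That the exclusions remove poor sleepers is plausible but carries no figure.
- **The floor is not absolute.** ISI 0–7 is a category, and a woman scoring 7 can still lose seven points. Two diets can also differ because one arm worsens, which a floor does not prevent.
- **The target population is legitimate.** The question concerns women with overweight or obesity, and the whole-group mean effect is a proper target. Requiring poor sleep at entry would be a design preference.
- **Subgroup work is planned.** The Statistical assessment section states "We plan to conduct two subgroup analyses, both with strong biological rationale and possible interaction effects", and provides for interaction tests. A reader might infer that poor sleepers will never be looked at separately. The variables are simply not named, and an article may leave that to the full protocol or analysis plan.

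What none of this touches is the explicit 80% claim for PSQI, ESS and ISI, which has no sleep input behind it.

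**Conclusion.** The concern holds as a point about the power statement. The 80% with 23 per group is reproduced for FFM (22.79, rounded up) and is unsupported for the three sleep outcomes. Because entry requires no sleep problem, their power could be much lower if many women have little room to improve.

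The size of the shortfall cannot be fixed from the document. It is about 15%, 28% and 45% under the four assumptions of Step 3, and roughly 26–75% when either the SD or the zero-effect assumption is relaxed as in Step 4. A sufficiently small SD would remove the shortfall altogether. These figures show how strongly the claim depends on inputs that the article does not supply. They do not estimate the trial's actual power. The enrolment rule itself is not an error.

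**What to change.** **Sample size calculation section.** Limit the 80% statement to FFM, at the unadjusted 5% level used. Alternatively, restate power for PSQI, ESS and ISI as an explicit assumption, giving a difference and SD for an unselected population together with the resulting range.

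**Same section or the Discussion.** State that a null sleep result in the whole group does not rule out a benefit in women with poor sleep at baseline.

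**Optional, Statistical assessment section.** Name baseline sleep score as one of the two subgroup analyses already planned. Fit it as an arm-by-baseline-score interaction in the ANCOVA, keeping the score continuous and using each outcome's own baseline. Report it with 95% confidence intervals as exploratory. Its precision will be low: Step 5 gives about 33% power even for the simple effect in poor sleepers at a one-third share.

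**Cost.** A few sentences. Baseline scores are already needed for the change outcomes, so no visit, participant or eligibility rule changes. The price is a less favourable power statement for sleep.

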### Randomization

Fifty-six participants will be selected from the Health Centers of Kashan University of Medical Sciences by Simple Random Sampling according to the inclusion and exclusion criteria. A trained nutritionist will enroll participants. Eligible participants will be stratified by age and BMI to ensure between-group homogeneity. Participants per stratum will be assigned to one of the two groups “modified intermittent fasting” (intervention) and “daily calorie restriction” (control) after baseline investigations. Individuals cannot be blinded to allocation because of the nature of the intervention. An independent statistician will generate the allocation sequence by using random numbers’ table and the statistician will be blinded throughout the entire trial.

### Sample size calculation

We based our sample size calculation on fat-free mass (FFM) data of a previously published randomized controlled trial [17]. The mean and standard deviation of FFM were 63.4 and 3.4 (kg) in the intervention group and 66.9 and 4.9 (kg) in the control group. To detect a clinically significant difference in the outcome measures (sleep quality, daytime sleepiness, insomnia, BMI, FFM, body fat mass, waist circumference, waist-to-hip ratio, hip circumference, the visceral fat area, percent body fat, soft lean mass, skeletal muscle mass, extracellular water ratio, and total body water) with an alpha error of 5% and power of 80%, 23 women will be needed in each group. We presume a drop-out rate of 20%, based on clinical study experience, and thus 28 women will be recruited in each group.$$n=\frac{{\left(Z1-\frac{\alpha }{2}+Z1-\beta \right)}^2\left({\sigma}_1^2+{\sigma}_2^2\right)}{\left({\mu}_1-{\mu}_2\right)}$$

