## Outcome measures

### Primary outcomes

The primary outcomes of the study are the differences between the two groups with regard to the changes from baseline values in the following variables: Pittsburgh Sleep Quality Index (PSQI), Epworth Sleepiness Scale (ESS), Insomnia severity index, BMI, FFM, body fat mass, waist circumference, and the waist-to-hip ratio.

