### Intervention

The flow chart of the intervention is shown in Fig. 2. In this study, 56 participants will be selected from the Health Centers of Kashan University of Medical Sciences by Simple Random Sampling according to the inclusion and exclusion criteria. Eligible participants will be stratified by age and BMI to ensure between-group homogeneity. Participants per stratum will be assigned to one of the two groups “modified intermittent fasting” (intervention) and “daily calorie restriction” (control) after baseline investigations. All participants will be required to follow their diet which is prescribed for 8 weeks based on their group and daily energy requirements. The energy requirements for the individuals will be calculated using the Mifflin equation [18]. Intermittent fasting will involve alternating periods of feeding and fasting, on an every-other-day basis (subjects will consume only 25% of the recommended calorie intake on the fasting days and then will consume 100% of the calculated daily energy requirements on feeding days). At midnight each day, the fast and feed days will begin. All fast day meals will be consumed as lunch between 12.00 pm and 2.00 pm to ensure that each subject will be undergoing the same duration of fasting. Participants will be permitted to drink energy-free beverages (such as water, tea, and green tea), coffee without sugar (<400 mg caffeine daily), and non-starchy vegetables (such as lettuce, green leaf, cucumber, and tomato). They will be encouraged to consume plenty of water. On feeding days, the participants will be provided foods at 100% of the calculated daily energy requirements (three main meals and three snacks) and will be advised to eat breakfast at 8:00, lunch at 13:00, and dinner at 20:00. Additionally, participants will be advised to have the first snack at 10:00, the second snack at 16:00, and the last snack at 22:00. The control group daily will consume 63% of their energy requirement (three main meals and three snacks) and will be advised to eat breakfast at 8:00, lunch at 13:00, and dinner at 20:00. Also, the first snack should be eaten at 10:00, the second snack at 16:00, and the last snack at 22:00. Both groups will follow their diet for 8 weeks. Control and intervention group subjects must prepare all their meals at home. All subjects in the two groups will be asked to keep their regular physical activity throughout the study. Daily dietary carbohydrates, fat and protein will account for 55, 30, and 15% of energy requirement, respectively. All participants will have the same number of contacts with the dietician at the on-site visits and phone visits for questions. Implementation adherence will assess by a food record questionnaire. It will be completed by the participants once every 2 weeks, 3 days (2 days/week and 1-day weekend) a week. If the total caloric intake of patients will be between 80 and 110% of the prescribed, there will be adequate adherence [19]. The following will be prohibited during the study: taking a special diet, taking a special supplement or medicine. An overview of the study design, interventions, and assessments to be conducted during the study and their timing is presented in Fig. 1 (enrolment, interventions, and assessments) and Fig. 2 (flow chart of the intervention).

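### The 80% power claimed for all 15 change-from-baseline outcomes is unsupported: the calculation uses one 3.5 kg difference in FFM levels and has no sleep or change-score inputs

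*Protocol article*

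**What the plan says.** The protocol's Sample size calculation section names a single source and a single variable: "We based our sample size calculation on fat-free mass (FFM) data of a previously published randomized controlled trial [17"]. The inputs are given as "The mean and standard deviation of FFM were 63.4 and 3.4 (kg) in the intervention group and 66.9 and 4.9 (kg"), the last pair being for the control group. The power statement is then made for a list of 15 variables, beginning "To detect a clinically significant difference in the outcome measures (sleep quality, daytime sleepiness, insomnia" and running through all eight primary and all seven secondary outcomes. Its conclusion is "with an alpha error of 5% and power of 80%, 23 women will be needed in each group", raised to 28 for drop-out, or 56 in total.

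The Primary outcomes section defines its endpoints as the "differences between the two groups with regard to the changes from baseline values", and the Secondary outcomes section uses the same definition. The Statistical assessment section plans analysis of covariance for the difference in changes, and a Bonferroni correction because there are several outcomes. It does not say over how many outcomes the correction runs.

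**The concern.** The calculation and the claim do not match in two ways.

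- **Scale.** Values of 63.4 and 66.9 kg can only be FFM levels, since no eight-week change is of that size. The endpoints are changes. The protocol gives no SD of change and no baseline to follow-up correlation, and no reason why a 3.5 kg gap between levels in another trial is the difference in FFM change to look for here.
- **Scope.** One FFM calculation is presented as giving 80% power for 14 further outcomes: the three sleep scales and 11 others. None of these has a stated target difference or SD, so the calculation contains nothing about sleep, which leads the title and supplies the first three primary outcomes.

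A reader will use the 80% figure to judge a non-significant sleep result. If the figure has no basis, such a result may be taken as stronger evidence of no difference than the design can provide.

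**Working it through.** **Inputs from the protocol.** FFM 63.4 (SD 3.4) and 66.9 (SD 4.9) kg; alpha 5%, two-sided because the printed formula uses Z at 1 − α/2; power 80%; 23 per group (Sample size calculation). Eight primary and seven secondary outcomes (Outcome measures). Bonferroni correction (Statistical assessment).

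**Step 1: reproduce the stated figure.** n = (1.960 + 0.842)² × (3.4² + 4.9²) / (66.9 − 63.4)² = 7.849 × 35.57 / 12.25 = 22.79, so 23. The stated number is therefore built from the gap between levels and the SDs of levels, for FFM only. (This needs the mean difference squared. The denominator as printed is not squared and would give 7.849 × 35.57 / 3.5 = 79.8, so the squared version was the one used.)

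**Step 2: the standardised difference behind it.** Root-mean-square SD = √(35.57/2) = 4.217 kg; d = 3.5/4.217 = 0.83. With the noncentral t distribution in place of the normal approximation, 23 per group reaches 80% power at d of about 0.84.

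**Step 3: what 23 completers per group give on any outcome** (two-sided t-test, noncentral t):

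| Alpha | d for 80% power | Power at d = 0.5 |
|---|---|---|
| 0.05 | 0.84 | 38% |
| 0.05/8 (primary outcomes) | 1.10 | 13% |
| 0.05/15 (all outcomes) | 1.17 | 9% |

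At unadjusted 5%, d = 0.3 gives 17% and d = 0.6 gives 51%. If all 28 per group completed, d = 0.5 would give 45%.

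**Step 4: FFM on the change scale.** With equal SDs at baseline and follow-up and correlation r, SD of change = 4.217 × √(2(1 − r)). The correlation is not in the protocol. Assumed values of 0.98, 0.95 and 0.90 give 0.84, 1.33 and 1.89 kg; an assumed 2.5 kg corresponds to r of about 0.82. The 1 kg target below is also an assumption.

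| Assumed SD of change (kg) | Power for 1 kg, 23 per group, alpha 5% | Detectable at 5% (0.84 × SD) | Detectable at 0.05/8 (1.10 × SD) |
|---|---|---|---|
| 0.84 | 98% | 0.7 kg | 0.9 kg |
| 1.33 | 70% | 1.1 kg | 1.5 kg |
| 1.89 | 42% | 1.6 kg | 2.1 kg |
| 2.5 | 26% | 2.1 kg | 2.8 kg |

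Power for FFM change thus runs from 26% to 98% over inputs that the protocol does not fix.

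**Step 5: the sleep scales.** No calculation is possible beyond the standardised differences in Step 3, because the protocol gives neither a target difference nor an SD for PSQI, ESS or the Insomnia Severity Index.

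**The case against.** Sizing a trial on one variable is common, and using levels is not an error in itself. Under randomisation the expected difference in final level equals the expected difference in change. Level SDs are conservative for a change score whenever the baseline correlation exceeds 0.5, and the planned analysis of covariance lowers the residual SD further. For FFM, then, the choice of SD may well have made the trial larger than needed. This stands, and it is why the finding is that the power is unsupported rather than too low. It does not supply a reason for 3.5 kg as the target, and it does not reach the other 14 outcomes.

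A reader might also infer more than the documents carry:

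- **That 3.5 kg is impossible here.** The diets are nearly matched in energy: alternating 25% and 100% averages 62.5%, and "The control group daily will consume 63% of their energy requirement". The Background also cites a "3 to 7% reduction in body weight under a fasting diet within 8 to 12 weeks". But that range reports earlier studies and is not this trial's stated expectation. Energy matching alone does not exclude a body-composition difference either; the Background cites an eight-week trial with greater fat and weight loss under fasting. The supportable statement is that 3.5 kg is not justified.
- **That the 3.5 kg was a baseline imbalance in the cited trial.** That report is not at hand, so this is conjecture.
- **That the gap runs in the wrong direction, with lower FFM under fasting.** The sign does not affect a two-sided sample size.
- **That a null sleep result could not be interpreted.** An estimate with its confidence interval remains interpretable whatever was assumed at planning. What fails is reliance on the 80% figure.

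**Conclusion.** The concern holds in this form. The 23 per group reproduces from FFM levels alone. The statement that it gives 80% power for 15 change-from-baseline outcomes has no basis in the protocol for the three sleep scales, for the other 11 outcomes or for any change score, and 3.5 kg is not justified as a difference in FFM change.

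What the number does support is 80% power for a standardised difference of about 0.84 at an unadjusted two-sided 5%. Under the protocol's own Bonferroni correction the figure is about 1.10 or 1.17, depending on whether eight or fifteen outcomes are counted. These values assume 23 completers per group, a two-sample t-test and no gain from covariate adjustment. The FFM range of 26% to 98% rests in addition on an assumed 1 kg difference and assumed SDs of change. No single corrected sample size can be derived from the document.

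**What to change.** Keep 56 women and rewrite the Sample size calculation section as follows.

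1. Delete the claim that the calculation covers all 15 outcomes.
2. State that 23 completers per group give 80% power only for a standardised difference of about 0.84 at an unadjusted two-sided 5%, and of about 1.10 at 0.05/8 (1.17 at 0.05/15) under the planned Bonferroni correction. Say which number of outcomes the correction uses. Quoting 0.84 alone would still overstate power for the analysis as planned.
3. Convert this into PSQI points and kg of FFM change by multiplying by an SD of change, either sourced or explicitly labelled as assumed. The protocol contains no such SD, so the authors have to supply it.

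Recruitment, allocation, visits and analysis are unchanged. The cost is rewording and the search for an SD of change; the downside is that the stated power becomes less favourable.
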